**Objective:**

The aim of this study is to compare the efficacy of a VR exposure-based intervention for public speaking anxiety and the level of VR presence between a 1-session treatment and an equal exposure time divided into 3 sessions, followed by 4 weeks of online intervention in both groups.

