Due to conflicting theoretical arguments for each condition’s superiority, we hypothesize that the 1-session and 3-session VR exposure for public speaking anxiety will differ in their efficacy without specifying which one will have the superiority. The aim of this study was to compare the efficacy of VR exposure-based intervention for public speaking anxiety and levels of VR presence between two conditions—one-session exposure and the same exposure time divided into 3 sessions, followed by 4 weeks of online intervention for both conditions.

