### Interventions

Some studies have found that 1 session of VR exposure plus 4 weeks of an online program for public speaking anxiety was effective in reducing public speaking anxiety [25,41]. A previous meta-analysis comparing one session to several sessions of in vivo exposure for specific phobias did not find a difference in effectiveness between the two [32]. However, because of the specificity of VR exposure and public speaking anxiety, it is unclear how dividing the same amount of exposure tasks into three 1-hour-long sessions, including 3 tasks each (which is a more typical duration for a therapy session), instead of one 3-hour-long session including a total of 9 tasks, would affect the effectiveness of VR exposure for public speaking. After the exposure sessions, a 4-week online program to encourage the transition to in vivo exposure for public speaking will be part of both conditions.

The VR exposure intervention for public speaking anxiety chosen for this study is based on established tasks and negative belief testing used in traditional cognitive behavioral therapy and exposure-based interventions for public speaking anxiety. The effectiveness of this type of intervention has been confirmed in previous studies [42,43]. The intervention consists of two parts: a face-to-face VR exposure session, which has been adapted and modified from a previous study by Lindner et al [43], and a 4-week online intervention developed by Lindner et al [43]. Participants will be randomized into two intervention groups, either consisting of 1 or 3 VR exposure sessions, cumulatively consisting of the same number of same-length exposure tasks. Both groups will participate in a 4-week online transition intervention after VR sessions.

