
In the group of the 3 VR exposure sessions, the same procedure will be applied, except that the same exposure tasks in the same order will be divided into the 3 sessions (first session: tasks 1‐3; second session: tasks 4‐6; third session: tasks 7‐9). All 3 sessions will be held over a period of 2 weeks. Psychoeducation will be provided only in the first session, and information about the importance of transition to in vivo exposure as well as an assessment of the convenience of the 3-session format will be done only in the last session. Exposure sessions will be conducted by trained clinical and health psychologists and psychology master’s students supervised by experienced psychologists.

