#### Other Outcome Measures

##### In-Session Assessments

A series of single-item measures will take place before and after the speaking tasks, as well as following the review of the audio recording. Each measure will be rated on a scale from 0 to 100, but using different verbal anchors at the extremes. The subjective level of distress (using the Subjective Units of Distress Scale [SUDS]), rated from “no distress” to “extremely high distress,” will be measured once the speaking task is presented to the participant and twice after the task is completed, asking the participant to indicate the SUDS after the task and the highest level reached during the task. Participants will also be asked to indicate their negative beliefs and expectations related to the task; that is, they will be asked to provide a qualitative description of their fears and concerns related to upcoming task performance, and then they will also be asked to rate the likelihood of these fears and concerns to become true from “definitely not going to happen” to “definitely going to happen,” and after the task was completed and the audio recording was reviewed, participants will once again rate to which extent their expectation has proven to be true from “not true at all” to “completely came true.” Furthermore, participants will be asked to rate the quality of their performance from “completely failed” to “completely succeeded” right after each task and following the review of the audio recording.

The sense of presence will be measured in two different ways. First, after each task, using a scale from 0 “definitely not” to 100 “definitely yes,” participants will be asked to rate whether they actually had the sense of “being there” while performing the speaking task in VR. Second, to assess the overall experience, the sense of presence of participants will be measured with the Igroup Presence Questionnaire (IPQ) [51]. Assessments will be taken after a 1-session VR exposure treatment in the 1-session condition or after each session in the 3-session exposure condition, and participants will be asked to answer questions about their sense of presence during the whole session. This questionnaire consists of 14 items measuring 3 subscales: spatial presence, involvement, and experienced realism. Each item is rated on a 7-point Likert scale, and the score is calculated by summing the ratings for each item. The scale previously showed good psychometric properties (α=.87) [52].

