### Statistical Analysis

The primary outcome will be a change in PSAS scores from baseline to posttreatment assessment (two primary endpoints: *t*_2_ and *t*_7_), as well as during follow-up assessments in both intervention groups. Secondary outcomes will be changes in secondary outcome measures from baseline to posttreatment and follow-ups. Repeated measures within-between ANOVA and effect sizes will be used to assess and compare outcomes within and between groups. The reliable change index (RCI) will be used as a supplementary analysis to analyze individual outcomes following intervention. No interim analyses or formal stopping rules were planned because this intervention is considered low-risk and is not expected to cause any harm to the participants. Regression analysis will be used to test the extent to which the level of anxiety and other psychological states measured by primary and secondary measures during baseline, sense of presence (IPQ at the end of the treatment), age, and gender, and user experience rated by participants predict the efficacy of the intervention. Single-item sense of presence after each task and user experience ratings of the format will be used for further exploratory purposes. In order to handle protocol nonadherence and missing data, it is planned that intention-to-treat will be the primary analysis approach, supplemented by additional per-protocol analysis. As recommended by the CONSORT (Consolidated Standards of Reporting Trials) guidelines, both analyses will be performed and reported for primary outcomes [57], allowing comparison of the effects of both approaches. Multiple imputation techniques will be used to fill in missing data.

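### The plan designates no like-for-like presence measure for its aim of comparing VR presence between arms, and the one IPQ score it names covers nine tasks in one arm and three in the other

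*Protocol article*

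**What the plan says.** The Objective in the abstract sets out to compare, alongside efficacy, "the level of VR presence between a 1-session treatment and an equal exposure time divided into 3 sessions". The end of the Introduction repeats this, naming "levels of VR presence between two conditions" as part of the aim.

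In-Session Assessments describes two presence measures. One is a single 0-100 item rated after every speaking task. The other is the 14-item IPQ, with this schedule: "Assessments will be taken after a 1-session VR exposure treatment in the 1-session condition or after each session in the 3-session exposure condition". Its reference period is the session just finished: "participants will be asked to answer questions about their sense of presence during the whole session".

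The sessions differ in content by design. The Interventions section contrasts three one-hour sessions of three tasks each with the single long one: "instead of one 3-hour-long session including a total of 9 tasks". VR Exposure Sessions keeps the tasks and their order the same in both arms and allocates them in the 3-session arm so that the last visit holds only the final three ("third session: tasks 7‐9").

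Statistical Analysis gives the two measures different roles. The IPQ enters a regression for efficacy as "sense of presence (IPQ at the end of the treatment", next to baseline measures, age, gender and user experience. For the other measure it says: "Single-item sense of presence after each task and user experience ratings of the format will be used for further exploratory purposes". It names no analysis that compares presence between arms.

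**The concern.** The one IPQ score that the plan singles out is not the same quantity in the two arms. In the 1-session arm it summarises the whole course of exposure. In the 3-session arm it summarises the last third. Any difference between arms in this score mixes the effect of spacing with which tasks were rated and how long a period was recalled.

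Two things are at stake. First, the efficacy regression would pool a predictor whose meaning depends on arm. Without arm in the model, its coefficient blends the association between presence and outcome within arms with whatever separates the arms. Second, an analyst who turns to the presence aim finds the unmatched score given the more prominent role and the task-matched rating set aside as exploratory. This matters because the Introduction itself suggests that presence may fade when tasks are repeated in one long session, and that lower anxiety might then reflect lost presence rather than learning.

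**Working it through.** **The plan's own figures.** The documents give no effect size, standard deviation or power for presence, so there is no presence figure to reproduce. The sample size of 86 concerns a repeated-measures ANOVA at three time points, none of which is an IPQ assessment. It reproduces (f = 0.25, three measurements, correlation 0.5, alpha 0.05: power 0.801 at N = 86), and nothing here depends on it.

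**Step 1: what the end-of-treatment IPQ covers.** This needs no assumption beyond reading the IPQ's session reference as written.

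| | 1-session arm | 3-session arm |
|---|---|---|
| Session preceding the last IPQ | the only session, about 3 hours | third session, about 1 hour |
| Tasks covered | 1 to 9 | 7 to 9 |
| Share of tasks | 9 of 9 | 3 of 9 |

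**Step 2: size of the artefact under a simple drift.** Assumptions: presence changes by b points per task, identically in both arms, and a session rating equals the mean over that session's tasks.

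- Mean task position for tasks 1 to 9: (1 + 2 + ... + 9)/9 = 5.
- Mean task position for tasks 7 to 9: (7 + 8 + 9)/3 = 8.
- Difference, 3-session minus 1-session: 8b − 5b = 3b.

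| Drift b per task | Apparent arm difference 3b | True arm difference |
|---|---|---|
| −1 | −3 | 0 |
| −2 | −6 | 0 |
| −3 | −9 | 0 |

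The values of b are illustrative points on a 0-100 scale. The factor of 3 holds on any scale on which b is expressed.

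**Step 3: the alternatives under the same assumptions.**

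- Mean of the three session scores: session means sit at positions 2, 5 and 8, so (2b + 5b + 8b)/3 = 5b. The difference from the 1-session score is 0.
- Per-task rating: each task is compared with the same task in the other arm, so the difference is 0 at every task.

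**Step 4: direction.** With fading presence (b negative), the artefact lowers the score of the 3-session arm. The Introduction's suggestion is that the long single session loses presence, which would lower the 1-session arm. The artefact can therefore hide or reverse the pattern that the authors suspect.

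**Step 5: the regression.** If the 3b shift were the same for everyone, an arm term would absorb it. If drift varies between participants, the 3-session score also carries each person's own drift, which an arm term does not remove. Hence both the averaged score and the arm term are needed.

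**The case against.** The strongest reply has four parts.

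- **A matched measure is collected.** The per-task rating exists for the same nine tasks in both arms, and the IPQ is taken after all three sessions, so a summary over all tasks can be formed. This stands. A reader might infer that the presence aim has no comparable data or is beyond answering, and the documents do not support that. The gap is that no such measure is designated for the aim.
- **The named IPQ score is a regression predictor.** A reader might infer that the plan will compare arms on the end-of-treatment IPQ. The article never says so. The mismatch applies directly to the regression, and to the presence comparison only if that score is carried over.
- **Presence has a modest role.** It sits under Other Outcome Measures, the trial calls itself exploratory, and the formal hypothesis concerns efficacy only. The remark about fading presence is conjecture in the Introduction. All true, but presence is still written into the aim in two places.
- **An article leaves model detail to an analysis plan.** This also stands in part. The missing arm term would not be a finding alone, and the general ANOVA sentence might be meant to reach further. However, that sentence follows outcomes defined as change from baseline, and presence has no baseline. The article also goes beyond silence: it names an IPQ time point and ranks the two measures, and its version history says that the choice of presence measure was clarified in version 1.3.

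Finally, preferring a single item to a 14-item scale is partly judgement, and the article reports psychometric support only for the latter.

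**Conclusion.** The point holds in this form: the plan states a presence comparison as an aim but assigns no like-for-like measure to it. The IPQ score that it does name covers 9 of 9 tasks in one arm and 3 of 9 in the other. The coverage mismatch follows from the text alone. The size of any resulting artefact, 3b, rests on an assumed common linear drift and on session ratings behaving as task averages. The documents give no value for b, so the 3 to 9 points are a range for illustration and not an estimate. Followed as written, the regression uses a predictor that is not comparable between arms. The presence aim is not answered by the analyses named, although the data collected could answer it. Neither the sample size nor the primary PSAS comparison is affected.

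**What to change.** For the presence aim, compare arms on the 0-100 rating over tasks 1 to 9, with arm, task and arm-by-task in a model that allows for repeated ratings within participants. The arm-by-task term shows whether presence changes differently over the sequence in the two arms.

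Wherever the IPQ is used, including the efficacy regression, take the mean of the three session scores in the 3-session arm and include arm in the model. State that three one-hour recalls are still not the same as one three-hour recall.

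Label the change post hoc. The Limitations section says that the team had already worked with the data and that final statistical decisions will be described in the results reports, so the change belongs there.

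Cost: analysis and reporting only, with no new data and no change in sample size. The downside is that the single item is less rich than the IPQ, which stays as supportive evidence.

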### Sample Size

Sample size was calculated for superiority analysis to test whether one condition shows bigger effects at least at the medium effect level. Power analysis was performed using the G*Power program for repeated measures ANOVA between factors’ effects, which showed that given a significance level of .05 to achieve 80% power to detect a medium between-groups effect (Cohen *f*=0.25) with 2 groups × 3 time measurements (pretreatment, 1 week post last exposure session, and at the end of the online intervention period or equivalent time), with an estimated correlation between repeated factors of 0.5, a total sample of 86 is needed.

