At the end of the 1-session format or before closing the last of the 3-session format, participants will be asked to evaluate the format of the intervention they participated in. Using a 7-point semantic differential type scale, the participants will be asked to rate their attitude and experience regarding 5 characteristics: convenience, duration, fatigue, intensity, and adaptability. The two groups will receive slightly different and specific parallel wording in the instructions. For the 3-session format, “You met the researcher three times and each session took about an hour, how would you rate that format?” while for the 1-session format, “You met the researcher one time and this session took about three hours, how would you rate that format?”

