## Results

### Recruitment

The recruitment to the study officially started in January 2024. As of November 2025, a total of 101 participants have completed the initial screening, of whom 37 met the inclusion criteria and were randomized. Recruitment of participants was still ongoing during the submission of this paper in December 2025. The final results of the study are expected to be prepared and submitted for publication in March 2026.

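### The secondary regression lists baseline PSAS as a predictor of a change measured from that same score, and mixes in postrandomisation, arm-dependent ratings without naming arm

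*Protocol article*

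**What the plan says.** In the Protocol article, Statistical Analysis, the relevant sentence opens "Regression analysis will be used to test the extent to which the level of anxiety". It goes on to list the other psychological states in the baseline primary and secondary measures, the IPQ at the end of treatment, age "and gender, and user experience rated by participants predict the efficacy of the intervention". The baseline primary measure is the PSAS. Randomised arm does not appear in the list.

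The sentence does not define efficacy. The same section does define the primary outcome: "The primary outcome will be a change in PSAS scores from baseline to posttreatment assessment". Primary Outcome Measures fixes the baseline as the PSAS from online eligibility screening. Participants and Eligibility Criteria admits only those scoring 60 or above on the PSAS.

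Two of the listed predictors are collected after randomisation. In-Session Assessments has the IPQ completed once in the 1-session arm and after each session in the 3-session arm. For the format, "the participants will be asked to rate their attitude and experience regarding 5 characteristics: convenience, duration, fatigue, intensity, and adaptability", with instructions worded differently for each arm.

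**The concern.** There are two separate problems.

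**Baseline PSAS.** If the dependent variable is change from the screening score, that score sits on both sides of the equation. Any error or short-term fluctuation in it pushes baseline and improvement in the same direction. Selecting on the same score adds regression to the mean for the group as a whole. A report could then say that more anxious students benefit more when they do not.

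**Presence and format ratings.** These are not pretreatment characteristics. They can depend on arm. If arm also affects the outcome and is not in the model, a rating with no effect of its own picks up part of the arm effect. A report could then say that presence or convenience predicts benefit when the rating is only marking which format was received.

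The trial's own premises make the second problem live. The Introduction hypothesises that the arms differ in efficacy, suggests that presence may fall during one long session, and makes comparison of presence between arms an aim.

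**Working it through.** **The plan's own figure.** The document gives no figure for the regression. Its sample size does reproduce. Sample Size gives alpha 0.05, 80% power, f=0.25, 2 groups and 3 measurements, "with an estimated correlation between repeated factors of 0.5, a total sample of 86 is needed". With λ = N·f²·m/(1+(m−1)ρ) and df = 1, N−2, N=86 gives λ = 86×0.0625×3/2 = 8.06 and power 80.1%; N=84 gives 79.2%. So 86 is the smallest even total. For two equal groups f=0.25 corresponds to d = 2f = 0.5. These values are used below.

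**Step 1: coupling.** Let baseline and post scores have equal variance and correlation r, with true change unrelated to true baseline, so that r acts as the reliability. Then

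corr(baseline, baseline − post) = (1−r)/√(2(1−r)) = √((1−r)/2).

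If selection cuts a normal baseline at its mean (an assumption; the document does not say where 60 falls in the screened population), baseline variance shrinks to k = 1 − 2/π = 0.363 of its value, and

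corr = (1−r)√k / √((1−r)²k + 1−r²).

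For r=0.5 this is 0.301/√(0.091+0.75) = 0.33. For r=0.93 it is 0.042/√(0.002+0.135) = 0.11.

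The range for r runs from the protocol's 0.5 up to 0.93, the internal consistency given for the Lithuanian PSAS, used here as the high end. The last two columns show how often baseline PSAS reaches p<0.05 at N=86 (4,000 simulated trials per cell).

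| r | Correlation, no truncation | Correlation, cut at mean | Significant, no truncation | Significant, cut at mean |
|---|---|---|---|---|
| 0.50 | 0.50 | 0.33 | 99.9% | 88% |
| 0.70 | 0.39 | 0.25 | 96% | 63% |
| 0.93 | 0.19 | 0.11 | 41% | 18% |

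**Step 2: how far the coupling spreads.** If post = a + b·baseline + c·rating + error, then post − baseline = a + (b−1)·baseline + c·rating + error. The coefficient c and its p value are identical in both forms. Coupling therefore distorts only the baseline PSAS coefficient.

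**Step 3: leaving out arm.** Trials were simulated with baseline–post correlation 0.5, an arm effect of d=0.5 on the outcome, and a rating that differs between arms but has no effect of its own. The rating differences are assumed. Change was regressed on baseline and rating, with and without arm (4,000 runs each).

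| Rating difference (SD) | N=86, no arm term | N=86, arm term | N=37, no arm term |
|---|---|---|---|
| 0.5 | 9.8% | 5.3% | 7.0% |
| 1.0 | 20.6% | 5.1% | 10.9% |
| 1.5 | 34.7% | 5.1% | 15.7% |

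At N=37 with an arm term the rate is 4.5% to 5.1%. N=37 is the number randomised by November 2025, with recruitment continuing, and not a stated analysis sample. If arm has no effect on the outcome, or the rating does not differ by arm, the rate without an arm term stays between 4.5% and 5.5%.

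**Step 4: content of the IPQ.** The IPQ asks about the whole session just completed. In the 1-session arm that is nine tasks. If the last administration is the one used in the 3-session arm, it covers tasks 7 to 9 only. The predictor would then differ in content by arm, apart from any true difference in presence.

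**The case against.** The strongest reply is that one sentence in a condensed article names predictors of interest and is not a model specification. That stands in part. A reader might infer that every listed variable enters a single model, and go on to work out how much variance so many noise predictors would explain. The section says only that regression will be used; separate or blockwise models fit it equally well. A reader might also infer that arm is certain to be left out. It is not listed, but the text does not exclude it. Nor does the sentence say that efficacy is the change score, although that is the natural reading given how the section defines the primary outcome.

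The size of the coupling is also open to challenge. The figure of 0.50 requires all of the imperfect correlation to be error. At r=0.93 it falls to 0.19, and truncation lowers it further. So the text does not support saying that a spurious baseline finding is almost certain. The format wording is described as parallel and only slightly different, and the Introduction says the effect of VR duration on presence is unclear, so a rating difference between arms is possible but not established.

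Finally, the analysis is secondary in a trial described as exploratory, and the Limitations section says more robust methods are being considered. That lowers the stakes. It does not answer the point, because the variables at issue are ones the protocol itself chose, and this regression is not among the weaknesses which that section acknowledges.

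**Conclusion.** The point holds as a flaw in a secondary analysis. As listed, the baseline PSAS coefficient cannot be read as showing who benefits. Its correlation with improvement under no true relation is 0.19 to 0.50 without truncation and 0.11 to 0.33 if the baseline is cut at its mean, over reliabilities of 0.93 to 0.5. Even at the low end it reaches significance in 18% of simulated trials at N=86. This rests on change from screening being the dependent variable.

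Presence and format ratings can stand in for arm, but only if arm affects both the rating and the outcome. On the assumed d=0.5 and rating differences of 0.5 to 1.5 SD, the false-positive rate at N=86 is about 10% to 35%, against about 5% with an arm term.

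A reader might go further and conclude that the whole regression yields spurious predictors, or that the trial's main result is compromised. Neither follows. Coupling touches one coefficient, the arm problem is conditional, and the primary between-group comparison is not affected.

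**What to change.** - Use the post-treatment PSAS as the dependent variable, with baseline PSAS and randomised arm in every model.
- Treat baseline PSAS as an adjustment variable and do not interpret its coefficient as a predictor of benefit.
- Report IPQ and format ratings in a separate arm-adjusted analysis, labelled associational and kept apart from the pretreatment predictors.
- State in the results report that this specification was made after data were seen, since the Limitations section says the team had already worked with the data.

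The cost is wording and one added model term. All the variables are already in the assessment schedule. The price in evidential standing is that the analysis must be presented as post hoc.
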